**Fig. 1 Fig1:**
[figure not shown]
Stepped wedge schedule for the QUILT study

### Eligibility criteria {10}

#### Inclusion criteria

all patients > 18 years of age undergoing mastectomy and/or axillary lymph node dissectionbe irrespective of the nature of the primary tumour: prophylactic, risk reducing, benign, in situ carcinoma and invasive primary or recurrent carcinoma will be eligible, irrespective of preoperative systemic therapy.

#### Exclusion criteria

patients who objected to participationmentally incompetent patients or otherwise unable to complete a questionnaireimmediate breast reconstructionpregnancy

### Who will take informed consent? {26a}

Quilting, or skin flap fixation, is an accepted suturing technique. Pre-operatively at the outpatient clinic, patients will be informed about the study by their treating surgeon or breast care nurse. In addition, an instruction is handed out on how to object to participation in the study if patients do not wish to receive questionnaires, object to have pictures taken or object to their medical data being processed for this study purpose.

### Additional consent provisions for collection and use of participant data and Biological specimens {26b}

All patients will receive a patient information form about the study with a letter of objection they can submit if they do not want to receive questionnaires, reject to have pictures taken and/or object to the processing of their medical data for this study purpose.

### Interventions

#### Explanation for the choice of comparators {6b}

Not applicable.

### Intervention description {11a}

After completion of the mastectomy, a breast field block using bupivacaine or ropivacaine is installed all around underneath the fascia at the edges of the wound. Traditional wound closure consists of closure of subcutaneous tissues using absorbable multifilament 2/0 running suture, and skin closure using 4/0 monofilament resorbable running suture.

The implemented intervention is the quilting suture technique (quilting). With quilting the subcutaneous tissue is sutured to the pectoralis muscle placing multiple rows of running sutures (absorbable, size 0). The suture starts at either end of the scar, running back and forth, creating rows of quilting stiches. The rows are placed transversely from the cranial to the caudal end of the wound with 2–3 cm between them, totalling some three to five rows for the cranial flap. The caudal flap is quilted with two to three rows in a caudal to cranial fashion. The redundant skin is trimmed away, resulting in a tight skin flap, sutured in a tension-free fashion consisting of a subcutaneous absorbable multifilament size 2/0 running suture followed by a 4/0 resorbable monofilament intracutaneous running suture. No wound drain is placed. Prophylactic antibiotics are not warranted, however, can be administered according to local protocol. Topical wound management consists of application of steri-strips. A tight fitting bra or bandage is recommended for the first postoperative days. Regular daily mobilization of the shoulder is stimulated, the first week with shoulder abduction limited to 90 degrees, thereafter without limitation.

### Criteria for discontinuing or modifying allocated interventions {11b}

Subjects can leave the study at any time for any reason if they wish to do so without any consequences. Surgeons can refrain from quilting sutures as deemed necessary or by lack of expertise, after which patients are excluded from participation (no cross over).

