### Objectives {7}

The objective is to report whether implementation of quilting in breast cancer surgery improves textbook outcome. Data is collected on the incidence of seroma and other postoperative complications, postoperative pain, shoulder function and health care consumption.

We hypothesize that implementation of quilting in breast cancer patients undergoing mastectomy and/or an axillary lymph node dissection increases textbook outcome. We expect incidences of seroma and other postoperative wound complications to decrease, with the same cosmetic outcome and without an increase in postoperative pain or impairing shoulder function. Moreover we hypothesize health care costs to reduce as a result of quilting.

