### Sample size {14}

To calculate the sample size of a randomized controlled trial TO is assumed to be 30% without quilting, as based upon a pilot study [7]. A doubling of TO is considered clinically significant, resulting in a TO of 60% with quilting. In this study 2 treatment arms will be used, with a significance level of 0.05 and power of 80%. For a parallel randomized trial in which *patients* are randomized, a minimum of 44 patients need to be included:$$2* {\left({\mathrm{Z}}_{\frac{0.05}{2}}+{\mathrm{Z}}_{0.80}\right)}^{2}*\frac{1}{{0.30}^{2}}* 0.45\left(1-0.45\right)=44$$

However, since in the present study *clusters* and not patients are randomized, we need to correct for the fact that outcomes within clusters are very likely more similar than those between clusters. The degree of similarity is estimated using the intra-cluster correlation coefficient (ICC) [35]. This was estimated to be on average 0.028, based upon the pilot study of the 2 hospitals with the variables age, body weight, ASA classification, type of surgery, neo-adjuvant chemotherapy, radiotherapy, tumour classification and first or second episode of breast cancer.

Consequently, the formula as proposed by Hemming et al. was used to correct for this similarity with a total of nine clusters and nine steps [36]. This led to a minimum of 94 patients in total or 11 per centre. A margin safety of 20% was introduced to correct for loss-to-follow-up, which led to a total of 113 patients or 13 per centre. Based on an average of 50 mastectomies each year per centre, the duration of the total inclusion should take 3 months. To correct for the probability of non-adherence to the quilting technique since it is new implemented for all surgeons (safety margin of 20%) each step will take 2 weeks. Suspected transition period and learning curve was suspected to be eight weeks.

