### Assignment of interventions: allocation

#### Sequence generation {16a}

At the beginning of the study all hospitals will be randomly assigned to a step. Randomization will be performed with an online randomisation tool by the lead investigator at the beginning of the study.

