### Implementation {16c}

Before the start of the study, the lead investigator visits each hospital to inform the professionals involved with breast cancer at the outpatient clinic of the department of surgery of participating hospitals. Implementation of quilting is monitored in each hospital, after randomisation quilting becomes standard practice and all patients undergoing mastectomy and/or axillary lymph node dissection will be quilted, including those individuals who decide not to participate in the study. The quilting technique is a straightforward technique and will be demonstrated and instructed to surgeons by video instructions. On request, surgeons are welcome to join a quilting procedure at the Canisius Wilhelmina Hospital and on site teaching can be provided by an experienced breast surgeon.

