### Assignment of interventions: Blinding

#### Who will be blinded {17a}

Not applicable, no blinding.

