### Methods in analysis to handle protocol non-adherence and any statistical methods to handle missing data {20c}

Stochastic regression imputation will be used to impute missing data.

Patients lost to follow up will be excluded from the study.

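### Patients whose surgeon does not quilt are excluded after allocation, and only in the quilting phase, so the primary comparison does not estimate the effect of implementing quilting and probably favours it

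*Protocol article*

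**What the plan says.** The rule stands in Criteria for discontinuing or modifying allocated interventions {11b}: "Surgeons can refrain from quilting sutures as deemed necessary or by lack of expertise, after which patients are excluded from participation (no cross over").

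The surrounding sections fix its context:

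- **Allocation comes first.** Sequence generation {16a}: "At the beginning of the study all hospitals will be randomly assigned to a step".
- **The aim is implementation.** Objectives {7}: "The objective is to report whether implementation of quilting in breast cancer surgery improves textbook outcome".
- **Intended coverage is complete.** Implementation {16c}: "after randomisation quilting becomes standard practice and all patients undergoing mastectomy and/or axillary lymph node dissection will be quilted".
- **The surgeon knows the condition.** Who will be blinded {17a}: "Not applicable, no blinding".
- **Non-adherence is foreseen.** Sample size {14}: "To correct for the probability of non-adherence to the quilting technique since it is new implemented for all surgeons (safety margin of 20" per cent), followed by the statement that each step lasts two weeks.
- **The section on non-adherence and missing data {20c}** gives stochastic regression imputation and one further rule: "Patients lost to follow up will be excluded from the study".

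Statistical methods {20a} specifies a logistic mixed model with a random intercept for cluster and names no analysis population. None of these sections brings non-quilted patients back into the analysis.

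**The concern.** The trigger for exclusion is a decision not to quilt, so it exists only after a hospital has crossed over. Patients for whom a surgeon would have held back, and patients of surgeons not yet proficient, stay in the conventional phase because nobody asks the question there. In the quilting phase they disappear. The two phases then differ in who is counted as well as in how the wound was closed, and the choice is made by someone who knows the condition.

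Two things are at stake. The first is the estimand. In a study of implementation, patients who end up not quilted are part of the result, and dropping them answers a different question. The second is bias. If those dropped have a worse outlook than average, the remaining quilting group looks better even when quilting does nothing.

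This is not a detail that can be left to a later analysis plan. The protocol states the exclusion itself, and if the excluded patients' outcomes are not collected, no later analysis can recover them.

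**Working it through.** **Inputs from Sample size {14}.** Textbook outcome 30% without quilting and 60% with it; two-sided alpha 0.05; power 80%; 44 from the individual-randomisation formula; 94 after the stepped-wedge correction; 113 after a 20% loss margin.

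**Reproducing the article's figures.** 2 × (1.960 + 0.842)² × 0.45 × 0.55 / 0.30² = 43.17, rounded up to 44. This formula gives a number per arm, and 44 is read that way below. 94 × 1.2 = 112.8, rounded to 113. The step from 44 to 94 could not be confirmed, because the article does not give the cluster-period size or the exact variant of the correction. Nothing in the bias calculation depends on it.

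**Bias from the exclusion.** Let p be the textbook outcome rate in the quilting phase had everyone been kept, f the share excluded, and q the rate among those excluded. Then

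retained rate = (p − f·q) / (1 − f), and bias = f·(p − q) / (1 − f).

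The article gives neither f nor q, so both are assumptions shown as a range. The value f = 20% is borrowed from the size of the planning margin. With no true effect (p = 30%):

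| f | q | Retained rate | Spurious difference (points) |
|---|---|---|---|
| 20% | 0% | 0.300/0.80 = 37.5% | +7.5 |
| 20% | 15% | 0.270/0.80 = 33.8% | +3.8 |
| 20% | 20% | 0.260/0.80 = 32.5% | +2.5 |
| 20% | 30% | 0.240/0.80 = 30.0% | 0 |
| 20% | 40% | 0.220/0.80 = 27.5% | −2.5 |
| 10% | 0% | 0.300/0.90 = 33.3% | +3.3 |
| 10% | 15% | 0.285/0.90 = 31.7% | +1.7 |
| 10% | 20% | 0.280/0.90 = 31.1% | +1.1 |

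An unclustered normal approximation was run with 47 control patients (half of 94) and 47 × 0.80 = 37.6 quilting patients. The two-sided false-positive rate is about 11% at f = 20%, q = 0%, and about 6% at f = 20%, q = 20%, against a nominal 5%.

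If quilting does work, with p = 60%, f = 20% and q = 30%, the retained rate is (0.60 − 0.06)/0.80 = 67.5%, an overstatement of 7.5 points.

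**What keeping these patients does to power.** Assume non-quilted patients have the 30% control rate. The quilting-phase rate is then 0.60(1 − f) + 0.30f, and the article's formula gives:

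- f = 5%: 58.5% v 30%; 47.7, so 48 per arm.
- f = 10%: 57% v 30%; 52.9, so 53 per arm.
- f = 20%: 54% v 30%; 2 × 7.849 × 0.42 × 0.58 / 0.24² = 66.4, so 67 per arm.

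At 44 per arm and 54% v 30%, the standard error is √(2 × 0.42 × 0.58/44) = 0.105, and 0.24/0.105 − 1.96 = 0.32, which is about 63% power without clustering. Scaling 94 in proportion gives 94 × 66.4/43.2 ≈ 145, or about 174 after the article's own factor of 1.2. That scaling is rough, since 94 itself was not reproduced.

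**The case against.** A reader might infer that the rule certainly biases the result towards quilting. The article does not support that. It says nothing about the prognosis of those excluded, and one of its two reasons, lack of expertise, concerns the surgeon and not the patient's risk. The table shows the bias vanishing or reversing for some values of q. What remains is an expectation about direction: removal on judged need or inexperience more plausibly takes out poorer outcomes than better ones.

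A reader might also infer that the plan expects 20% of patients to be excluded. It does not. The figure is a safety margin, used in setting step length; it is neither a forecast nor a ceiling for surgeon exclusions. The article also foresees an eight-week transition or learning period. How those weeks enter the analysis cannot be told from the text, and the schedule figure is not available. If they are set aside, many exclusions for lack of expertise would fall outside the comparison and 20% would be too high.

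It is tempting to call the statement in Implementation {16c} that "all patients undergoing mastectomy and/or axillary lymph node dissection will be quilted" a flat contradiction of the exclusion rule. It is better read as hospital policy with an exception stated elsewhere. The mismatch with the objective is the firmer argument. Nor is the randomisation undone: the order of hospitals stays random, and the damage is selection of patients within that order.

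Finally, q = 0% is an extreme, and even 7.5 points is small beside the planned 30-point difference. That is fair as to size. It does not answer the objection that the estimand has changed.

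**Conclusion.** The point holds in this form: the protocol prescribes a post-allocation exclusion that can act only in the quilting phase, is decided without blinding, and is reversed nowhere in the article. This much follows from the text and needs no assumption. The resulting contrast is per-protocol on one side only and does not match an objective framed as implementation.

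That it favours quilting is likely but unproven. Its size depends on two unknowns, the share excluded and their prognosis. Over the range examined with no true effect, exclusion of 10% to 20% with below-average prognosis (0% to 20% textbook outcome) produces a spurious gain of about 1 to 7.5 points. That is modest against the planned effect, but enough at the upper end to roughly double the false-positive rate in an unclustered approximation.

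**What to change.** Replace the exclusion with an analysis rule, for example: *All eligible patients who do not object are followed and included in the primary analysis according to the condition allocated to their hospital on the day of surgery, whether or not quilting was performed, subject to the trial's handling of the transition period. Use of quilting and any reason for refraining are recorded.* Report the analysis restricted to patients actually quilted as a sensitivity analysis, with the number and reasons for not quilting by hospital. The surgeon's discretion to refrain is a clinical matter and is left as it is; only the consequence for follow-up and analysis changes.

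The cost is more than a sentence. Most components of textbook outcome come from the patient file, but the analgesic component compares six-month with pre-operative use, which is collected by questionnaire. Non-quilted patients must therefore stay in questionnaire follow-up as well. The estimate will also be diluted by non-adherence. The existing margin for non-adherence went into step length and not into the assumed effect, so the sample size section should restate power under a stated non-adherence rate.

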### Strategies to improve adherence to interventions {11c}

The quilting technique is a straightforward technique and will be demonstrated and instructed to surgeons by video instructions. On request, surgeons are welcome to join a surgical procedure at the Canisius Wilhelmina Hospital and on site teaching can be provided by an experienced breast surgeon.

### Relevant concomitant care permitted or prohibited during the trial {11d}

Preoperative indication for the operation will be conducted in accordance with the Dutch guidelines, within a frame of mutual shared decision making, supported by a multi-disciplinary team meeting. There are no rules of behaviour for study participants other than described in the “Intervention description” paragraph added to the local protocol following surgery. All concomitant care is permitted during the study, no limitations are imposed.

### Provisions for post-trial care {30}

Not applicable. The quilting suture technique is already a standard surgical technique. Also patients who do not participate in this study (wishing to refrain from filling out questionnaires) are quilted after implementation of the quilting technique in the participating hospitals. The burden of participation consists of filling out questionnaires and the pictures of the breast that are made during follow-up.

### Outcomes {12}

#### Primary study parameter/endpoint

‘Textbook outcome’ (TO), a combination of outcome parameters reflecting an ideal surgical outcome. Measured 6 months post-operative, the patients postoperative course must comply with the following to meet the definition of TO:no wound complicationsno re-admissions in relation to primary surgeryno re-operation in relation to primary surgery, re-excisions in case of involved margins allowedno unscheduled visit to the outpatient clinic (depending on the centre one or two postoperative visits are usually scheduled)postoperative use of analgesics (6 months) is not increased compared to pre-operative

#### Secondary study parameters/endpoints

Wound complications are defined by the Clavien Dindo classification of Surgical Complications [27] and scored when necessitating (bed side) treatment or follow-up with additional visits to the outpatient clinic, also if beyond 30-days postoperative.All palpation-detected seromas (non-aspirated), proportion (%)Clinical significant seroma (aspirated seroma), proportion (%)Surgical site infections (SSI), proportion (%)Wound hematoma or bleeding, skin flap necrosis, wound dehiscence, visualized by inspection, proportion (%)

Health care consumption:Duration of surgery: time from incision till wound closed (minutes), meanDuration of hospital stay (treatment in day care or amount of nights, day care classified 0), meanNumbers of unscheduled visits to the outpatients clinic (one postoperative visit is scheduled), medianReadmission to the hospital related to primary surgery, medianReoperation, related to primary surgery other than re-excision, median

Baseline characteristics based on assumed risk factors for formation of seroma [3, 4, 28–31]:Biological gender, proportion (%)Age (years at day of surgery), meanBMI (kg/m^2^), meanWeight of the removed breast (gram), meanPolypharmacy (use of five or more medications daily [32], proportion (%)TNM classification (type 1 to 4, no malignancy, in situ, ypT0N0, angiosarcoma), nominal, proportion per stage (%)Type of surgery (uni- or bilateral mastectomy, ALND or a combination), nominal, proportion per type (%)Prior irradiation of the breast in recurrent breast cancer, proportion (%)Neoadjuvant chemotherapy, proportion (%)

Other:Shoulder function questionnaire (DASH questionnaire = Disability of the Arm, Shoulder and Hand [33], median scorePost-operative pain (visual analogue scale day 1–14 postoperative and use of analgesics), median scoreCosmetic outcome (an independent panel of four surgeons will blindly assess cosmetics by classifying standardised digital photographs one a 4-point Likert scale with the following categories: poor, fair, good and excellent. Photos are taken in two positions: the first in neutral position with both arms hanging next to the body and the second with both arms raised in 180gr (or as far as possible) elevation).Satisfaction with thoracic wall (BreastQ questionnaire for mastectomy [34]), median score

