Despite the first report of success from quilting sutures in 1993, this technique is still not embedded in global daily practice [23]. Surgeons are reluctant to implement the quilting technique because of hypothetical disadvantages of quilting. In the absence of well-founded studies, critics are raised such as increased postoperative pain and decreased shoulder function caused by tight sutures, concerns exist about cosmetic outcome and possible skin dimpling and longer operating time could give raise to increased healthcare costs [16, 24].

To date, no multicenter prospective studies have been published in which quilting without postoperative wound drain is compared with conventional wound closure with postoperative wound drain, reporting on seroma and other potential (dis)advantages.

The objective of this study is therefore, to assess the impact of quilting in patients undergoing mastectomy and/or ALND in nine teaching hospitals. Postoperative complications, shoulder function, cosmetic outcome, satisfaction with thoracic wall, postoperative pain and healthcare consumption of patients treated with the quilting suture technique without drain will be compared with conventional wound closure. All these will be summarized in the primary outcome as textbook outcome. Textbook outcome is achieved if a patient suffers no wound complications, requires no re-admissions or re-operation in relation to primary surgery nor any unscheduled visit to the outpatient clinic and the postoperative use of analgesics after six months is not increased compared to pre-operative.

Textbook outcome is defined as the percentage of patients for whom all desired short-term outcomes of care are realized [25]. This outcome provides a meaningful summary measure of health care quality for patients, providers and insurance companies. It is a useful outcome to make a comparison between different hospitals. Usually significant variability between hospitals can be expected, all scoring well on different single factors, but poorly in other factors. Besides, a compound indicator reflecting the ideal surgical outcome is more meaningful than one single outcome item and it is a useful tool for managing patient expectations [26].

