### Participant timeline {13}

Participation burden consists of filling out questionnaires. The first questionnaires (t = 0 pre-operative) are handed out pre-operatively, (DASH, use of analgesics, BreastQ). Patients are asked to notate the VAS daily during the first two weeks postoperative. Two weeks postoperatively, at scheduled postoperative evaluation, participants will be evaluated by physical examination, a picture of the amputated breast will be taken by the treating surgeon or breast cancer nurse, combined with the DASH questionnaire and use of analgesics again (t = 1). Follow-up lasts for 6 months postoperatively when another picture of the amputated breast is taken and the final DASH and analgesic are completed (t = 2). Additionally, the BreastQ mastectomy module is questioned (Table 1).

**Table 1 Tab1:** Participant timeline

	**Enrolment**	**Operation**	**Days 1–14 postoperative**	**2 weeks postoperative**	**6 months postoperative**
Patient information form	X				
Letter of objection	X				
Physical examination				X	X
Picture of the thoracic wall				X	X
Questionnaires - DASH - Use of analgesics - Breast Q	X			X	X
VAS pain scores			X		

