### Statistical methods

#### Statistical methods for primary and secondary outcomes {20a}

Primary outcome is a binary outcome presented as number of cases and percentage. Nominal data will also be presented as percentage. Continuous data will be presented as mean ± standard deviation or median ± interquartile range, based upon whether the assumption of normality holds (visual interpretation). Analysis of continuous data will be performed by applying the Students T-test for unpaired data in case of continuous variables with a normal distribution. Otherwise the distribution will be compared using the Mann–Whitney U-test. Chi2 test will be used for comparisons of categorical variables between the two groups. The Fisher’s exact test will be performed where applicable. Since data is clustered analysis will be performed using a generalized logistic mixed-effects model with cluster as random intercept. A P-value < 0.05 is considered statistically significant.

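### The label median score for 14 daily VAS pain scores leaves the summary open, and the stated two-sample tests do not suit repeated scores per patient

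*Protocol article*

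**What the plan says.** In the protocol article, Participant timeline {13} sets the data collection: "Patients are asked to notate the VAS daily during the first two weeks postoperative". That is up to 14 scores per patient.

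Secondary study parameters/endpoints, under Other, gives the endpoint as "visual analogue scale day 1–14 postoperative and use of analgesics), median" score. One label covers the VAS series and analgesic use together.

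Statistical methods for primary and secondary outcomes {20a} treats the median as a way of presenting continuous data: "Continuous data will be presented as mean ± standard deviation or median ± interquartile range, based upon whether the assumption of normality holds". Normally distributed outcomes go to an unpaired t-test. For the rest, "Otherwise the distribution will be compared using the Mann–Whitney U-test", with P < 0.05 as the threshold. The same section adds: "Since data is clustered analysis will be performed using a generalized logistic mixed-effects model with cluster as random intercept". No term for patient or for day is named.

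Pain matters to the trial's question. Background {6a} lists among surgeons' reservations "increased postoperative pain and decreased shoulder function caused by tight sutures", and Objectives {7} expects the benefit to come "without an increase in postoperative pain or impairing shoulder function".

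**The concern.** The named tests take one independent value per patient and the data are a series of 14. Something has to happen to the series before either test can be applied, and the article does not say what. Three routes are open: test each day, pool all scores, or reduce each patient to one number. They behave very differently.

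The mixed-model sentence does not close the gap. A logistic model does not apply to a VAS score. Even if it is read generously as a mixed model suited to each outcome, its only random effect is the hospital, so a patient's 14 scores would still be treated as independent within the hospital.

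At stake is the answer to one of the stated reservations about quilting. Depending on the route taken, a chance difference could be reported as significant in either direction, or a null result from an insensitive summary could be read as reassurance.

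**Working it through.** **Inputs.** From the article: up to 14 daily scores per patient, P < 0.05, and 94 patients before the loss-to-follow-up margin (Sample size {14}), so 94 / 2 = 47 per condition if evenly split. The article gives no VAS mean, SD, time course or effect, so there is no figure of its own to reproduce and every VAS value below is an assumption. Hospital clustering is left out throughout.

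Assumption set A: VAS falls from about 4 to 1, between-patient SD 1.3, within-patient SD 1.0. Assumption set B: daily means 4.5, 4.2, 3.8, 3.4, 3.1, 2.8, 2.6, 2.4, 2.2, 2.0, 1.9, 1.8, 1.7, 1.6, between-patient SD 1.5, within-patient SD 1.2.

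**Route 1: a test on each day.** Were the 14 tests independent, the chance of at least one P < 0.05 with no true difference would be 1 − 0.95^14 = 1 − 0.488 = 51%. Scores within a patient are positively correlated, so the true figure is lower. Simulation gives 26–30% under set A, 30% under set B, and up to 48% across the other SDs tried. An early rise is not hidden on this route: under set B, a 2-point rise on days 1–3 shows as differences in group medians of about 2.0 on those days and about 0 from day 4.

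**Route 2: all scores pooled into one test.** Approximate check under set B:
- Variance of the daily mean profile over the 14 days: 0.847.
- Total variance of a pooled score: 1.5² + 1.2² + 0.847 = 4.537.
- Variance a pooled test assigns to a patient's mean: 4.537 / 14 = 0.324.
- Actual variance of a patient's mean: 1.5² + 1.2²/14 = 2.353.
- Ratio: 2.353 / 0.324 = 7.26, so the test statistic has SD √7.26 = 2.69 instead of 1.
- Type I error: 2 × [1 − Φ(1.96 / 2.69)] = about 47%.

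Simulating the Mann–Whitney test gives 46% under set B, 45–46% under set A, and 31–48% across all SDs tried.

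**Route 3: one 14-day median per patient.** Type I error is about right (4.5–5%). The weakness is sensitivity. The median of 14 values is the mean of the 7th and 8th in order. In the set B mean profile these are 2.4 and 2.6, so the median is 2.5. Adding 2 points to the first 6 days or fewer leaves both values in place, a shift of 0.0. Adding it to 7 days gives 2.4 and 4.6 (median 3.5, shift 1.0), and to 8 days 4.4 and 4.6 (median 4.5, shift 2.0).

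| Assumed rise | Set | Per-patient median: power | Comparator: power |
|---|---|---|---|
| +1.5, days 1–4 | A | 8% | first-week mean 88% |
| +1.0, days 1–7 | A | 32–35% | first-week mean 94–95% |
| +2, days 1–2 | B | 4% | day 1–3 mean 97% |
| +2, days 1–3 | B | 5% | day 1–3 mean 100% |
| +2, days 1–5 | B | 19% | day 1–3 mean 100% |
| +2, days 1–7 | B | 81% | day 1–3 mean 100% |

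With the SDs varied, the +1.5 rise on days 1–4 is detected in 8–26% of trials by the per-patient median and in 76–98% by the first-week mean. The comparators do well partly because their window overlaps the days on which the rise was placed.

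**The case against.** A reader might infer that the protocol collapses each patient's 14 scores to one median and so hides exactly the early pain that surgeons fear. The article does not support this. In the endpoint list nearly every item carries an across-patient summary: age and BMI, with one value per patient, are labelled mean, and DASH, taken at three time points, carries the same median score label. The statistics section also uses the median for presenting groups. A group median per day is therefore at least as natural a reading, and it hides nothing. Nor does Background {6a} place the feared pain in the first days; a short early rise is a scenario added here.

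It can also be said that the choice of days and summary for a secondary outcome belongs in an analysis plan that is not shown, that the article never proposes pooling, that the daily scores are kept, and that the sizes follow from assumed values.

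Much of this stands. It removes any claim that masking is planned and leaves the sizes as illustrations. It does not remove the mismatch. The article does name tests, and they do not suit repeated scores. The by-day reading escapes masking but brings 14 tests at an unadjusted threshold.

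**Conclusion.** The point holds as an ambiguity combined with an unsuitable stated analysis. The endpoint label does not say whether the median is per day across patients or over days 1–14, and the t-test or Mann–Whitney test does not suit 14 correlated scores per patient.

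By-day testing carries roughly a 26–48% chance of at least one false positive, and pooling roughly 31–48%. A within-patient median would keep its error rate but have low power for a rise of a few days. That last route is the only one of the three at risk of masking in this way, and the article does not state it. The figures depend on assumed VAS levels, SDs and time course, on 47 patients per condition, and on ignoring clustering; the zero shift for rises of up to six days also assumes steadily falling pain.

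This is worth correcting because pain is a named reservation about the technique. It does not affect the primary outcome.

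**What to change.** Analyse the daily VAS with one repeated-measures linear mixed model: day as a factor, technique, technique-by-day, and random effects for patient and hospital. Add calendar period because of the stepped-wedge design; the article's own model has only a cluster random intercept, so this term cannot be carried over from it. Name in advance one contrast, either overall or over a stated window of days, and report it with its 95% CI as the single pain comparison. Show medians by day for each technique descriptively, without tests, and reword the endpoint label to match. Summarise analgesic use separately, since Table 1 does not schedule it daily.

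The cost is analysis wording and one model, as the scores are already collected. The small downside is that the window must be fixed beforehand, and a wide one may dilute a rise lasting only a day or two; the descriptive daily profile would still show it.
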